### 3.3 Competent Ethics Committee

The ethics committee responsible for this study is the Ethics Committee of the Medical University of Innsbruck

### 3.4 Study registration

After receiving a positive vote from the ethics committees of the Medical University of Innsbruck, the study will be prospectively registered in the DRKS, ISRCTN or a comparable WHO-recognised registry.

### 3.5 Timetable

#### Study-related:

Recruitment period: 8 months

15.04.2021 Planned start: First Patient First Visit (FPFV)

15.11.2021 Last Patient First Visit (LPFV)/Last Subject In (LSI)

14.12.2021 Planned end: Last Patient Last Visit (LPLV)/Last Subject Out (LSO)

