#### Patient-related:

Active intervention duration: 4 weeks

After inclusion, the duration of each participant's participation will be 8 weeks (baseline survey, 4-week intervention, post-intervention testing, focus group for intervention group 1 participants only, follow-up call 4 weeks after the end of the intervention). The total duration of the study will be 8 months.

Figure 1 presents the patient-related study process.

[figure not shown]

**Figure 1:** Patient-related study procedure

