#### **4.1.2.3 Number of participants and sample size**

For this study, 34 people with Idiopathic Parkinson's Syndrome will be included. Of the 34 people with Parkinson's disease, 17 will be randomised to intervention group 1 and 17 to control group 2.

According to Julious, participants per group are considered a minimum sample size for a pilot study. (Julious, 2005) while Browne specifies a number of participants of 30 for a two-arm study. (Browne, 1995). Therefore, to evaluate the feasibility criteria and preclinical effects of the experimental intervention compared to the conventional control intervention, a sample size of 34 is aimed for, based on 30 participants, including an expected failure rate of 10% and using the formula  $N = n / (1 - (z/100))$ . Here, n is the number of participants (30) and z is the expected failure rate (10%).

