#### **4.4.14 Feasibility of a larger study**

##### **4.4.14.1 Feasibility criteria**

The feasibility criteria for a larger study are defined as follows:

- a) a target recruitment rate of 40% of 85 eligible patients (or 4-5 participants per month); the total number of eligible PD patients was estimated based on the number of eligible PD patients treated at RZM in the last 3 years.
- (b) a target retention rate of 80%,
- (c) a minimum target adherence rate of 75% (at least 3 out of targeted 4 practice sessions per week; documented in the CRF).
- (d) high safety of the intervention, no severe side effects or only very mild and transient side effects (continuously collected by means of UE log in CRF; see also chapter 4.5.2)
- (e) high acceptance of the intervention, continuously evaluated narratively during the intervention period and through focus groups with semi-structured questions (see chapter 4.4.14 and CRF for a detailed description of the focus groups and the questions asked).

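### The planned end of study is about four weeks too early for the last follow-up call, and the stated recruitment and total durations do not fit the timetable's own dates

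*Protocol*

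**What the plan says.** The study-related timetable in section 3.5, repeated in the synopsis, has four entries:

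- For the length of recruitment it states "Recruitment period: 8 months".
- The opening date for entry is given as "15.04.2021 Planned start: First Patient First Visit (FPFV").
- The closing date for entry is given as "15.11.2021 Last Patient First Visit (LPFV)/Last Subject In (LSI").
- The end of the study is then set at "14.12.2021 Planned end: Last Patient Last Visit (LPLV)/Last Subject Out (LSO").

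The patient-related part of the same section gives each participant 8 weeks from inclusion and closes with: "follow-up call 4 weeks after the end of the intervention). The total duration of the study will be 8 months". Table 1 in section 4.2.1 lists the call as a scheduled contact 4 weeks after the end of the intervention, and section 4.3.2 places it two months after baseline. Table 2 and section 4.4.13 make the call the source of the follow-up FOGQ, FES-I and falls.

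Three further statements bear on the consequences. Section 4.1.2.3 derives 34 patients from 30, "including an expected failure rate of 10" per cent. Section 4.4.14.1 sets as feasibility criteria "a target recruitment rate of 40% of 85 eligible patients (or 4-5 participants per month") and "a target retention rate of 80" per cent. Section 5.6.1 counts as retained those who finish the study, without naming the visit, while Table 2 marks retention at both post-intervention and follow-up.

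**The concern.** The last-subject-out date should be the last subject's entry date plus the participation time, and it is not. The gap is about the length of the follow-up period, so the date appears to have been set from the post-intervention test. The recruitment and total durations do not repair this, because they disagree with the dates and with each other.

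What is at stake is the follow-up data of late entrants. FOGQ and FES-I at follow-up feed the Kruskal-Wallis analysis, and follow-up falls feed the Chi-square analysis, both in section 5.6.1. If the end date were applied as written, these data would be missing for a reason unrelated to feasibility, and retention measured at the call would be lowered by the calendar.

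The recruitment criterion raises a related question. It offers a percentage and a monthly rate as alternatives, and whether the two agree depends on how many months recruitment really lasts.

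**Working it through.** **Plan's own sample size.** 30 / (1 − 0.10) = 33.3, rounded up to 34. This reproduces, and 0.40 × 85 = 34 agrees with it. The planned N is not in question.

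**Last contact.** The inputs are the last first visit on 15.11.2021 and 8 weeks (56 days) of participation, both from section 3.5.

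- 15.11.2021 + 56 days = 10.01.2022. If the 8 weeks are counted from the first intervention day, one day after baseline as in Table 1, the date is 11.01.2022.
- 10.01.2022 − 14.12.2021 = 27 days (28 on the second count).
- 15.11.2021 + 29 days = 14.12.2021, which is about when the last patient's post-intervention test falls.

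**Durations.**

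- 15.04.2021 to 15.11.2021 is 214 days, or 7.0 months, against 8 stated for recruitment.
- 15.04.2021 to 14.12.2021 is 243 days, or 8.0 months, which matches the stated total but omits the last follow-up period.
- 15.04.2021 to 10.01.2022 is 243 + 27 = 270 days; 270 / 30.44 = 8.9 months.
- A full 8 months of recruitment from 15.04.2021 would end on 15.12.2021. Adding 56 days gives 09.02.2022, about 9.9 months in total.

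**Patients affected if the end date were a hard stop.**

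- Latest entry that still reaches the call: 14.12.2021 − 56 days = 19.10.2021.
- Share of the window after that date: 27 / 214 = 12.6%.
- With uniform accrual (an assumption): 0.126 × 34 = 4.3 patients. At 4 to 5 per month, the last 27 days bring 3.5 to 4.4.

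**Effect on retention.**

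- Counted at the call, from the date alone: 1 − 0.126 = 87.4%. With exactly 4 lost it is 30/34 = 88.2%.
- Counted at post-intervention: no effect.
- Losses needed to miss 80%: 7 of 34, since 27/34 = 79.4% and 28/34 = 82.4%. That is 7 / 4.3 = 1.6 times the expected number cut off.
- With the 10% failure rate added: 0.874 × 0.90 = 78.6%, or 87.4% − 10% = 77.4% if the losses simply add.

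**Monthly target against 40% of 85 (34 patients).**

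| Rate per month | 7 months | 8 months |
|---|---|---|
| 4 | 28 (32.9% of 85) | 32 (37.6%) |
| 5 | 35 (41.2%) | 40 (47.1%) |

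The rate that yields 34 is 34/7 = 4.86 or 34/8 = 4.25 per month.

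**The case against.** The best defence is that 14.12.2021 marks the last in-person visit, leaving only a 15-minute telephone call. The date does coincide with the last post-intervention test, and the span from 15.04 to 14.12 is the 8 months given as the total. The date is also only a planned one. Section 5.5 lists no calendar cut-off among the reasons for ending the study, and Table 1 schedules the call for every participant, so in practice the calls would probably be made after 14.12. The primary endpoint is measured only at baseline and post-intervention.

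Much of this stands, and it limits the consequence: the loss of follow-up data is what the dates imply if followed, not what must happen. It does not rescue the date. The entry is labelled as the last subject leaving the study, and the same section has that subject participating for four more weeks. Nor does it explain 8 months of recruitment between dates 7 months apart.

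On the thresholds, the defence is stronger. The 10% is an expected loss used to inflate N, while the 80% is a feasibility target, and a target may reasonably be looser than an expectation. The monthly figure can be read as a rough restatement of 34, since 4.25 and 4.86 both lie within it, and section 5.6.1 evaluates recruitment as consented over eligible. What remains is that the lower end of the range falls short of the percentage it is offered as an alternative to.

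**Conclusion.** The timetable is wrong as stated. The end date is about 27 days too early for the participation period, the recruitment duration exceeds the span of its dates by a month, and the total cannot contain the stated recruitment plus 8 weeks. These follow from the protocol's own figures without assumptions. The possible loss of follow-up data for about 12.6% of the accrual window, roughly 4 of 34 patients, rests on uniform accrual and on no calls being made after 14.12.2021.

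A reader might infer that the date by itself pushes retention below 80%. It does not: the result is about 87% at the call and no change at post-intervention. A figure of 77% to 79% needs four things together: the 10% failure rate on top, uniform accrual, completion counted at the call, and no calls after the planned end. The protocol fixes neither of the last two.

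A reader might also infer that 80% retention contradicts N = 34, because 0.80 × 34 = 27.2 is below 30, and that the target should be 30/34 = 88%. The protocol uses 30 as a guideline number for sizing the pilot and does not make 30 completers a condition of success, so that is a preference and not an error.

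The monthly-rate point is secondary and holds only at the lower end: 4 per month gives 28 to 32 against 34.

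**What to change.** 1. Move the last-visit/last-subject-out date to no earlier than about 10.01.2022 if the last first visit stays at 15.11.2021, in both section 3.5 and the synopsis.
2. Restate the durations to match: 7 months of recruitment and about 9 months in total. If 8 months of recruitment is what is meant, move the last first visit to about 15.12.2021 and the end to about 09.02.2022.
3. Report retention separately at post-intervention and at follow-up, as Table 2 already marks it, and say which of the two the 80% criterion refers to.
4. Replace the monthly range with 34 divided by the actual recruitment months: 4.86 over 7 months or 4.25 over 8.

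Closing enrolment on 19.10.2021 to keep the present end date is not a good alternative. It leaves 187 days, or 187 / 30.44 = 6.1 months, and would need about 5.5 patients per month, above the protocol's own range.

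If the last first visit stays at 15.11.2021, the cost is a few text edits and about four more weeks of telephone calls. The planned N and the 80% target need not change.

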#### Patient-related:

Active intervention duration: 4 weeks

After inclusion, the duration of each participant's participation will be 8 weeks (baseline survey, 4-week intervention, post-intervention testing, focus group for intervention group 1 participants only, follow-up call 4 weeks after the end of the intervention). The total duration of the study will be 8 months.

Figure 1 presents the patient-related study process.

[figure not shown]

**Figure 1:** Patient-related study procedure

## **4 Methods**

### **4.1 Study participants**

#### **4.1.1 Participant recruitment and study inclusion**

All persons with Idiopathic Parkinson's Syndrome treated at the Reha Zentrum Münster during the recruitment period will be reviewed by the medical staff with regard to their suitability for study participation. All persons with idiopathic Parkinson's syndrome who meet the inclusion criteria of this study and do not fulfil any of the exclusion criteria will be informed about the study orally and in writing by the respective investigator. After determining a basic suitability (inclusion criteria) and the patient's consent, i.e. his/her interest in participating in the study, a screening is carried out. Using predefined cut-off scores of the Mini-Mental-Status-Test (MMST) (Folstein et al., 1975)  $\geq 24/30$  points, moderate to severe cognitive impairment is excluded. In the case of the absence of these exclusion criteria, study inclusion will be as described below.

After an appropriate reflection period, opportunity for questions and the patient's consent to participate, the information letter and patient consent form is then dated and signed by both the patient and the doctor. The investigator records the participation on a special patient identification list. This list is used to identify the patient at a later date and contains the patient's identification number (ID), full name, date of birth and date of inclusion in the clinical trial. The patient identification list remains at the trial site after completion of the trial. The ID will be entered with the date of inclusion in the randomisation list as described and prepared by an independent researcher.

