#### **4.1.2 Study population**

##### **4.1.2.1 Inclusion criteria**

Men and women with Idiopathic Parkinson's Syndrome using the UK Brain Bank criteria. (Hughes et al., 1992)(stages 1-3 according to Hoehn & Yahr) with ON medication. (Hoehn and Yahr, 1967), age 30-80 years, any ethnicity, ability to walk without an assistant, Mini-Mental Status Test (MMST)  $\geq 24/30$  (Tombaugh and McIntyre, 1992)Stable dosage of dopaminergic

replacement therapy at least 3 weeks before the start of the study or still without dopaminergic treatment for the duration of the study intervention, written and spoken German.

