### 4.2 Intervention

#### 4.2.1 Treatment scheme

The study includes a screening, a baseline examination, 16 intervention sessions a' 30 min over 4 weeks, a post-intervention testing, a focus group for the participants of the intervention group and a follow-up call 4 weeks after the end of the intervention.

The duration and number of examinations and treatments (Table 1) will take place in the context of the patients' inpatient interdisciplinary rehabilitation. It is ensured that all study participants receive the same number of treatments in total. In addition, all participants must receive 8 30-min sessions of physiotherapy per week, of which 4 are reserved for the study intervention in group 1 or 2 and represent an additional measure. All therapists will be trained on the study interventions and instructions for participants in both groups and will therefore work according to the same principles.

**Table 1:** Treatment regimen of a (screened possible\*) study participant

| Intervention                | Dosage | Time                                                                      | Duration    |
|-----------------------------|--------|---------------------------------------------------------------------------|-------------|
| Screening*                  | 1x     | After verification of suitability by the investigator and patient consent | 10-15 min   |
| Study inclusion             |        |                                                                           |             |
| Baseline investigation      | 1x     | Day 0 after study inclusion                                               | 75-90 min   |
| Intervention groups 1 and 2 | 16x    | Start on day 1 after the baseline examination                             | 30 min each |

|                          |    |                                                                                                                                           |           |
|--------------------------|----|-------------------------------------------------------------------------------------------------------------------------------------------|-----------|
|                          |    | 4 x per week, 4 weeks in total                                                                                                            |           |

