#### **4.4.3 Mini Mental Status Test (MMST)**

The MMST (Folstein et al., 1975) is used to assess cognitive function (temporal and spatial orientation, memory, attention, speech and language comprehension, also reading, writing, drawing and arithmetic) and serves as a screening tool for this clinical study.

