## 5.6 Data analysis

### 5.6.1 Statistical data analysis

Statistical data analysis is performed using IBM SPSS software, version 26.0 (IBM Corporation, Armonk, NY, USA) and Tobii Pro Lab Analyser (Tobii, Danderyd, Sweden). The statistical significance level is defined by a p-value of  $<0.05$ . An attempt is made to avoid missing data by inspecting the questionnaires after completion and, in case of unanswered items, asking the study participants to complete them. The number of missing data is noted; due to the less sensitive topic of the study, it is assumed that missing variable values can be assigned to "missing completely at random" or "missing at random". An intention-to-treat analysis is performed for all cases analysed in their originally assigned group.

Descriptive statistics are used for demographic data and primary and secondary outcomes. Counted and nominal scaled data (gender, fall rate, recruitment, retention and adherence rate, number of missing data if applicable, number of adverse events) are reported as whole numbers or percentages. Ordinal scaled variables (MMSE, UPDRS, H & Y, FGA, BBS, PDQ-39, FOGQ, FES-I, BDI-II) are expressed as median (minimum, maximum or interquartile range) and metric variables (TUG, TUGman, FSST, 10MWT, eye movements: Saccade velocity, amplitude, latency, fixation duration) by mean (95% confidence interval, CI or standard deviation, SD). The data is also presented graphically (e.g. by bar charts, box plot or line graphs).

The eligibility rate (%) is the percentage of patients suitable for the study after applying the inclusion and exclusion criteria from the Parkinson's patients treated at the Reha Zentrum Münster during the study period.

The recruitment rate (%) is determined as follows:  $(N_{\text{Consent}}/N_{\text{eligible}}) \times 100$ ; where  $N_{\text{Consent}}$  is the number of participants who signed the informed consent form;  $N_{\text{eligible}}$  is the number of patients eligible for the study based on the inclusion and exclusion criteria.

The retention rate (%) is calculated as follows:  $(N_{\text{completed}}/N_{\text{Total}}) \times 100$ ; where  $N_{\text{completed}}$  is the number of participants who completed the study;  $N_{\text{Total}}$  is the total number of participants in the study.

Adherence rate (%) is determined as follows: (Actual number of exercise sessions/planned number of training sessions)\*100 (Osterberg & Blaschke, 2005).

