### **6.3 Patient information and consent form**

Prior to the start of the trial, all patients must declare their consent in writing to the investigators after they have been fully informed in verbal and written form about the nature, significance and implications of the clinical trial in a manner that is comprehensible to them. The content of this information shall be documented on the informed consent form. Patients will be informed if significant new findings about the tested intervention arise during the trial.

The patient's declaration of consent to participate in the clinical trial is dated and signed by the patient and the doctor. The patient is given one copy of the signed information letter and consent form for participation in a clinical trial for patients. The second copy is filed by the doctor in the trial folder.

Participants will also be provided with a consent form for audio recording during the focus groups. If several participants refuse, one or more focus groups will be conducted without audio recordings, with field notes only.

It is expressly pointed out that no examinations of any kind may be carried out in connection with the study until a legally valid declaration of consent has been obtained from the patient.

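### Section 4.1.1 places the MMST screening before the signed consent that section 6.3 requires; once the order follows 6.3, the recruitment-rate formula also needs repair

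*Protocol*

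**What the plan says.** **Consent and screening.** Section 4.1.1 has medical staff review all Parkinson's patients at the centre and inform suitable ones orally and in writing. It then equates consent with interest and goes straight on to the MMST: "his/her interest in participating in the study, a screening is carried out". Only in the next paragraph, after a reflection period and time for questions, does it say that "the information letter and patient consent form is then dated and signed by both the patient and the doctor".

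Section 6.3 requires that, before the trial starts, "all patients must declare their consent in writing to the investigators after they have been fully informed". It adds that "no examinations of any kind may be carried out in connection with the study until a legally valid declaration of consent has been obtained".

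Section 4.4.3 says the MMST "serves as a screening tool for this clinical study". Table 1 in section 4.2.1 times the screening as "After verification of suitability by the investigator and patient consent", ahead of study inclusion, without saying whether that consent is written.

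**Recruitment rate.** The synopsis and section 5.6.1 divide N_Consent by the number of patients eligible on the inclusion and exclusion criteria. N_Consent "is the number of participants who signed the informed consent form". Section 4.1.2.1 lists an MMST of at least 24/30 among the inclusion criteria. Section 5.6.1 attaches a Wilson 95% interval to the rate. Section 4.4.14.1(a) sets the target at 40% of 85 eligible patients, or 4-5 participants per month.

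**The concern.** Two sections of one protocol give different orders for consent and a study test. Under 4.1.1 a cognitive test done for the study may precede the signature, and its purpose is to identify patients with impaired cognition. Under 6.3 that is prohibited. Staff and monitors need one rule.

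The second issue follows from settling the first. Signing becomes possible before eligibility is complete, yet the recruitment rate still counts every signature against a denominator restricted to fully eligible patients. Recruitment is the first feasibility criterion listed for the larger trial, so its observed value should be well defined.

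**Working it through.** **Step 1: the order of events**

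| Place | What must come before the MMST | When the form is signed |
|---|---|---|
| 4.1.1 | Information and expressed interest | After the MMST and a reflection period |
| Table 1 | Suitability check and consent of unstated form | Not stated |
| 6.3 | Full information and legally valid consent, which the section requires in writing | Before any study-related examination |

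Section 4.4.3 makes the MMST a procedure of this study, and Table 1 schedules it as a separate screening step. Nothing in the protocol says the score is taken from routine records. The 6.3 prohibition therefore covers it, and 4.1.1 conflicts with 6.3. Table 1 cannot settle the matter, because 4.1.1 uses the word consent for interest.

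**Step 2: the plan's own figures**

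- Sample size (4.1.2.3): 30 / (1 - 0.10) = 33.3, rounded up to 34.
- Target (4.4.14.1): 0.40 x 85 = 34, and 34 / 85 = 40.0%.
- Monthly rate: 34 / 8 months = 4.25, within the stated 4-5.

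The target reproduces and equals the planned sample.

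**Step 3: the formula under each order**

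Let E be signers who meet all criteria, F signers who fail the MMST, and N patients eligible on all criteria.

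- Order of 4.1.1 (test, then sign): those who fail do not go on to sign. The rate is E / N, and the numerator lies inside the denominator.
- Order of 6.3 (sign, then test): the rate is (E + F) / N. The F patients are not part of N. The excess over E / N is F / N.

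A Wilson interval presupposes that the numerator counts members of the denominator. That fails whenever F > 0.

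**Step 4: size under the 6.3 order**

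With N = 85 the excess is 1 / 85 = 1.18 percentage points per failure. The protocol gives no MMST failure rate, so the share of signers who fail is an assumption, shown from 0 to 20%. With 34 randomised, the signers needed are 34 / (1 - share), rounded up:

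| Assumed share failing | Signers | Observed rate on 85 | Excess over 40.0% (points) |
|---|---|---|---|
| 0% | 34 | 40.0% | 0 |
| 5% | 36 | 42.4% | 2.4 |
| 10% | 38 | 44.7% | 4.7 |
| 15% | 40 | 47.1% | 7.1 |
| 20% | 43 | 50.6% | 10.6 |

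**Step 5: what 85 denotes**

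Section 4.4.14.1 bases the 85 on eligible patients treated over the previous 3 years, which predates any study MMST. It does not say whether the 85 is net of the MMST criterion. If the 85 are counted before the MMST and 3 are known to fail (assumption), the formula's denominator is at most 82, and 34 signers give 34 / 82 = 41.5%. The table is therefore a guide to scale only.

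**The case against.** The best defence is that 6.3 is an express prohibition and Table 1 puts consent before screening, so 4.1.1 may be no more than a loosely worded clause. Figure 1, which could not be read for this review, may show the order. That limits what can be claimed. A reader might infer that every screened patient will be tested without written consent, but the protocol shows a contradiction, not a practice. The conflict in the text still has to be removed.

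Three other stronger readings are tempting and not supported:

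- **That the 40% figure depends on the order.** The target is 34 of 85 either way. Only the observed rate compared with it can shift.
- **That the formula fits neither order.** Under 4.1.1 every signer has passed the MMST, so the numerator is contained in the denominator. Patients who decline are never tested, but that is true of any uptake rate with a test reserved for interested patients. Section 4.1.1 already has staff review everyone for suitability, which makes a denominator from clinic review the natural reading.
- **That a wrong rate would decide whether the larger trial goes ahead.** Section 4.4.14.1 lists targets without a stop rule, and gives a monthly alternative that does not use this denominator.

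It is also fair to say that failures may be few, since dementia is an exclusion criterion and staff review suitability before patients are approached.

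**Conclusion.** The contradiction between 4.1.1 and 6.3 stands on the text alone, needs no assumption, and should be corrected.

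The recruitment-rate point is smaller and conditional. Under the order that 6.3 requires, signers who fail the MMST enter the numerator but not the denominator. This raises the observed rate by about 1.2 points each on a denominator of 85, and by nothing if none fail. The total cannot be fixed from the protocol, because it gives no failure rate and does not say whether the 85 is counted before or after the MMST.

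**What to change.** 1. Reword 4.1.1 and Table 1 so that the reflection period and signature precede the MMST, in line with 6.3. Oral and written information already comes first and need not move. In Table 1, state that the consent is written.
2. In the synopsis, 4.4.14.1(a) and 5.6.1, define the denominator as patients eligible on clinic review before the MMST, and make the numerator a subset of it. The Wilson interval then applies.
3. State that the target of 40% of 85 (34, the planned sample) refers to patients randomised.
4. Report the numbers signed, failing the MMST and randomised as separate counts, so that willingness to take part and screen failure can be told apart.

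The cost is wording only. The downsides are small: some patients will sign and then be screened out, and the reported rate may be slightly lower.
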